#### Definition of the ITT population

As recommended by ICH E9 guidelines [20], the primary analysis will be conducted according to the intention-to-treat principle, using the full analysis set (FAS). The ITT includes all randomized patients, except those with critical protocol deviations that prevent any valid post-randomization analysis. Specifically, the following patients will be excluded:Those who did not meet key eligibility criteria (i.e., major inclusion/exclusion violations)Those who did not receive at least one dose of the investigational treatmentThose with no post-randomization data available

This definition is consistent with the ITT approach, which aims to preserve the advantages of randomization while ensuring sufficient data are available for meaningful analysis.

#### Definition of relevant intercurrent events

The estimand of interest targets the effect of treatment on the time to clinical improvement within 30 days of randomization. The variable is defined as the time (in days) from randomization to clinical improvement, with a maximum follow-up of 30 days. Death before improvement is considered an intercurrent event and will be handled using a composite strategy, whereby death is interpreted as a failure to improve. In this case, the time to improvement will be right censored at day 30. Other intercurrent events are considered irrelevant to the definition of the treatment effect and will be addressed using a treatment policy strategy, meaning that patients will be analyzed according to their randomized treatment regardless of these events.

The treatment effect will be summarized by the adjusted hazard ratio with corresponding 95% confidence intervals.

#### Clinical secondary outcomes

Status severity score at day 7 will be compared between groups using a Cochran-Mantel-Haenszel test stratified on center.

Length of stay (from treatment administration to hospital discharge) and duration of O_2_ supplementation will be compared between groups using a linear regression model adjusted on center. The Huber-White method will be used to compute a robust variance estimator of the coefficients. Depending on the number of deceased patients, competitive risk analyses may be preferred to a linear regression model. Risk of in-hospital clinical failure will be compared between groups using a Cochran-Mantel-Haenszel test stratified on center. Risk difference and relative risk stratified on center will be estimated using the Mantel-Haenszel method.

Mortality and risk of influenza-related complications at day 90 will be compared between groups using a Cochran-Mantel-Haenszel test stratified on center. Risk difference and relative risk stratified on center will be estimated using the Mantel-Haenszel method.

Mean number of antibiotic days (AD) for respiratory illness will be compared between groups using a linear regression model adjusted on center.

Quality-of-life score at D90 will be compared between groups using a linear regression model adjusted for center and quality-of-life score at baseline.

#### Virology secondary outcomes

Proportion of patients with detectable RNA on day 3 post-treatment administration will be described using counts and percentages.

Proportion of patients with RNA detection and proportion of patients with an infectious viral load at day 3 post-treatment will be compared between groups using a Cochran-Mantel-Haenszel test stratified on center.

RNA and infectious viral load on day 3 (expressed in CT value and copies/ml and viral titer) will be compared between the two groups using a linear regression model adjusted for center and baseline viral load.

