**Methods:**

This is an investigator-initiated, randomized, triple-blind, placebo-controlled, superiority, multi-center trial to assess the clinical efficacy of single-dose baloxavir in decreasing time to clinical improvement in adult immunocompetent patients hospitalized with influenza. Patients (*n* = 484) with confirmed, severe infection (NEWS2 score ≥ 4) will be recruited over three influenza seasons in four large Swiss hospitals. Primary outcome: time to clinical improvement (in hours), calculated from treatment administration until NEWS2 score ≤ 2 maintained for 24 h or until hospital discharge, whichever comes first. The primary outcome is calculated in all patients independently of the duration of symptoms at treatment administration, as well as in participants treated early (<72 h) post onset of symptoms. The main secondary outcomes are the risk of serious influenza complications, length of hospitalization, and difference in viral load at D3 post-treatment administration.

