a: 1/8 h up to 10 days. If hospitalization is longer and the primary endpoint is still not reached, decrease NEWS2 score measurements to 1/day up to discharge. b: only if requested by the treating physician. c: only CRP and white blood cell count will be collected and only twice during hospitalization, first at D0 and second if available between D2 and D4. d: ±1 day. e: only if RT-PCR positive with CT value compatible with viral growth (CT value < 30). f: depending on budget availability. (x): 6 ml, only at HUG, only consenting participants accepting blood sample collection for future research, timepoint of collection ± 1D. *: All SAE will be collected and reported in the annual safety report. SARS and SUSAR will be reported timely to the regulatory authorities

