#### Virology outcome measures

Viral shedding is measured by RT-PCR test and is expressed in CT values or copies/ml. Data is generated at the Laboratory of Virology of the Geneva University Hospitals and will be entered to the e-CRF by the study nurses/physician or directly by the biologist in charge or a trained laboratory technician.Viability and infectiousness of the virus detected in the samples is measured by viral culture (expressed as a titer) at the Laboratory of Virology of the Geneva University Hospitals. Results will be entered to the e-CRF by the study nurses/physician or directly by the biologist in charge or a trained laboratory technician.

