### Methods in analysis to handle protocol non-adherence and any statistical methods to handle missing data {20c}

As our primary outcome is based on data collected during regular care of hospitalized patients, we do not expect to have missing data.

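### Day-3 viral titre will exist only for swabs with CT below 30, so the planned linear regression, if fitted to the titres that exist, is biased toward no difference

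*Protocol article*

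**What the plan says.** Three parts of the protocol article bear on this.

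- **When culture is done.** Table 1 (Participant timeline {13}) schedules viral culture on day 0 and day 3. Footnote e restricts it: "only if RT-PCR positive with CT value compatible with viral growth (CT value < 30").
- **What culture yields.** Under Virology outcome measures: "Viability and infectiousness of the virus detected in the samples is measured by viral culture (expressed as a titer"). RNA is measured separately and without a CT threshold: "Viral shedding is measured by RT-PCR test and is expressed in CT values or copies/ml".
- **How day 3 is analysed.** Under Virology secondary outcomes, the quantities to be analysed are given as "RNA and infectious viral load on day 3 (expressed in CT value and copies/ml and viral titer"). The method named for all of them is the same: they "will be compared between the two groups using a linear regression model adjusted for center and baseline viral load". The binary versions go to a center-stratified Cochran-Mantel-Haenszel (CMH) test: "Proportion of patients with RNA detection and proportion of patients with an infectious viral load at day 3 post-treatment will be compared".

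The abstract counts "difference in viral load at D3 post-treatment administration" among the main secondary outcomes, and infectious viral load on day 3 is a listed virology outcome. The missing-data section {20c} covers only the primary outcome: "As our primary outcome is based on data collected during regular care of hospitalized patients, we do not expect to have missing data". No section says how an uncultured or PCR-negative swab enters the virology analyses.

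**The concern.** Whether a patient has a day-3 titre depends on that patient's day-3 CT. If baloxavir lowers viral load, more baloxavir than placebo swabs will reach CT 30 or turn negative, and those swabs have no titre. The remaining swabs are the high-virus tail of each arm, and the tails resemble each other more than the arms do. Ordinary linear regression uses only rows with a value, so its default behaviour compares the tails.

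Two related gaps follow. The covariate is called baseline viral load without saying which measure; if it is baseline titre, patients with day-0 CT of 30 or more also leave the model. And the proportion with infectious virus depends on whether uncultured swabs stay in the denominator.

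At stake is a falsely weak result on infectious virus, for a trial whose secondary objectives include the duration of infectiousness.

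**Working it through.** The article gives no CT distribution, virology effect size or virology power, so there is no planned figure to reproduce. **Every CT and titre input below is an assumption.**

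**1. Direction, by hand.** Take day-3 CT as normal with SD 5, placebo mean 29.5, and a drug shift of 3 CT (baloxavir mean 32.5). With z = (30 − mean)/SD, the cultured share is Φ(z) and the mean CT among cultured swabs is mean − SD·φ(z)/Φ(z).

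| Arm | z | Cultured share Φ(z) | Mean CT if cultured |
|---|---|---|---|
| Placebo | (30 − 29.5)/5 = 0.1 | 0.54 | 29.5 − 5 × 0.397/0.540 = 25.8 |
| Baloxavir | (30 − 32.5)/5 = −0.5 | 0.31 | 32.5 − 5 × 0.352/0.309 = 26.8 |

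A true difference of 3 CT shrinks to about 1 CT among cultured swabs, before baseline adjustment.

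**2. The same case on the titre scale, adjusted for baseline CT.** By simulation: CT0 ~ N(25, 5); CT3 = 0.6·CT0 + 14.5 + shift + N(0, 4); log10 titre = max(0, (36 − CT3)/3.3 + N(0, 0.7)). The latent effect for 3 CT is 3/3.3 = 0.91 log10.

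| Analysis, 3-CT shift | Estimate (log10) |
|---|---|
| All swabs, had all been cultured | −0.74 |
| Cultured swabs only | −0.39 |
| All swabs, uncultured set to 0, linear regression | −0.80 |
| Tobit, uncultured censored at 0 | about −1.8 |

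Cultured-only keeps 0.39/0.74 = 53% of the all-swab figure. With 400 swabbed patients, power is about 62% cultured-only and nearly 100% with all swabs kept.

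**3. How far this depends on the assumptions.** A second simulation varied placebo mean day-3 CT (24 to 33), shift (1.5 to 5 CT), SD (4 or 6) and baseline correlation (0.3 or 0.6), with 0.3 log10 titre per CT and residual SD 0.8. Share of the latent effect kept by the cultured-only regression:

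| Placebo mean CT | Share kept |
|---|---|
| 24 | 0.54 to 0.80 |
| 27 | 0.41 to 0.62 |
| 30 | 0.28 to 0.45 |
| 33 | 0.18 to 0.35 |

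The share is below 1 in all 48 scenarios. Setting uncultured swabs to a floor of 0 gives ratios of 0.51 to 1.57 to the latent effect, so the floor value itself matters.

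**4. What the CT rule does not reach.** CT and copies/ml exist for every PCR-positive swab, and RNA detection for every swab tested. Regression on CT or copies/ml still has no value for PCR-negative swabs; restricted to positive swabs, it keeps 58% to 100% of the CT effect in the same scenarios (PCR limit assumed at CT 40).

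**The case against.** The strongest reply is that the article states no exclusion. The threshold is justified as the range in which virus can be expected to grow, which suggests that swabs at CT 30 or above are regarded as negative, and the binary outcome is a proportion of patients, not of cultured swabs. Assigning values to samples below a limit is commonly left to the analysis plan, which is not shown, and a floor value fits the text. This stands in part: a reader might infer that these patients are dropped by design, and the article does not say so. But it fixes both the culture rule and the regression, and the two do not fit together without a further rule. In the example above, the two compatible readings differ about twofold (−0.39 against −0.80).

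Three other strong readings are tempting and not supported:

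- **That the effect is halved.** This holds in some scenarios only; the documents give no CT data.
- **That the whole day-3 virology result is affected.** Only culture-based outcomes are. The abstract's viral load need not mean titre.
- **That patients with CT 30 or above have cleared the virus.** Many are still RNA-positive, and placebo patients reach that range too.

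It is also fair to object that linear regression need not be abandoned. With a floor it came close to the all-swab figure in the example (−0.80 against −0.74). A Tobit model censored at zero titre roughly doubled the latent effect (about −1.8 against −0.91), because in that model a swab at CT 30 has an expected titre of (36 − 30)/3.3 = 1.8 log10, well above zero.

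**Conclusion.** The point holds for day-3 viral titre, and for the proportion with infectious virus if uncultured swabs leave its denominator. Fitted to existing titres, the named model conditions on a post-randomization variable that the drug is meant to change, and the titre comparison is biased toward no difference. The direction was the same in every scenario tried, given that titre falls as CT rises and that the drug raises CT. The size is not fixed by the documents: roughly 20% to 80% of the effect is kept, depending on how many swabs fall below CT 30. It concerns a secondary outcome and leaves the primary analysis untouched, but it should be settled before unblinding because the choice of handling can change the result materially.

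**What to change.** State the following in the protocol or analysis plan:

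1. All patients with a day-3 swab enter the virology analyses.
2. Swabs that are PCR-negative or have CT of 30 or more count as having no infectious virus and stay in the CMH denominator.
3. Titre is compared by a rank-based analysis with uncultured swabs in the lowest category. Acceptable alternatives are linear regression on log10 titre with a pre-specified floor value, or a censored model whose limit corresponds to the CT 30 culture threshold and not to zero titre.
4. The baseline covariate is day-0 CT, available for every patient with a positive day-0 PCR, and not day-0 titre.
5. PCR-negative day-3 swabs are given a stated value or rank in the CT and copies/ml comparisons.

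The cost is wording only, with no new samples or cultures. The downside is an assumption that swabs at CT 30 or above carry less infectious virus than cultured ones; this is in line with the article's own threshold, but the trial will not test it, since those swabs are not cultured.

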#### Safety secondary outcomes

SAEs unrelated to the natural course of a severe influenza infection, SAR, and SUSAR will only be described as count and/or percentage. As we do not expect them to happen, no comparison is planned between the 2 groups.

### Interim analyses {21b}

We will perform a blinded sample size re-estimation after the second influenza season. The objective will not be to evaluate the treatment effect, but to check the basis of our sample size calculation (median time to clinical improvement and prevalence of patients with symptoms evolving for less than 72 h). No other interim analysis is planned.

Early termination of the trial: Decision about early trial termination is the responsibility of the Safety Monitoring Board (SMB). If any safety signals suggest that withholding antiviral treatment could endanger participants, or if new research findings (from randomized, placebo-controlled trials in hospitalized adults) demonstrate the benefits of antiviral therapy in this population, the SMB will determine whether early termination of the study is necessary.

### Methods for additional analyses (e.g., subgroup analyses) {20b}

Subgroup analysis: using the same approach as in the primary analysis, the clinical efficacy of baloxavir in decreasing time to clinical improvement compared to placebo will be assessed in the following subgroups: patients with symptoms evolving for less than 72 h at treatment administration.

### Methods in analysis to handle protocol non-adherence and any statistical methods to handle missing data {20c}

As our primary outcome is based on data collected during regular care of hospitalized patients, we do not expect to have missing data.

### Plans to give access to the full protocol, participant-level data and statistical code {31c}

The full protocol is accessible on demand at any time upon request to the principal investigator. Datasets originating from our project and used in case of the publication of our results will be deposited in the institutional open-access data repository: “Dryad” and will be made public at the time of the publication. Metadata will be searchable and discoverable.

## Oversight and monitoring

### Composition of the coordinating center and trial steering committee {5d}

The composition of the coordinating center, roles and responsibilities: The coordinating PI who is also the sponsor representative and the trial coordinator who is also a Co-PI are managing the trial at the Geneva site as well as at all the other Swiss recruiting centers. There are 9 other Co-PIs at the coordinating site. Four of them are responsible for patient recruitment, others are responsible for the oversight of the sample analysis at the Geneva University Hospitals’ Virology Laboratory, others are responsible for the oversight of the study’s biobank, and others have support function due to their extensive experience in RCTs. The trial does not have a steering committee.

Trial guidance: At the coordinating center, the coordinating PI and the trial coordinator assume the day-to-day support for the trial. They meet with the local PIs and the study nurses at the three other Swiss centers weekly online to discuss and resolve any issues concerning patient inclusion, follow-up, safety measures, and data entry to the e-CRF. The study coordinator connects daily with the study nurses at the coordinating center for the same purposes as detailed above. Outside of flu season, the coordinating PI, the study coordinator, and the local PIs meet every second week to discuss questions concerning study design, regulatory authorities’ submissions, and other fundamental study issues.

Handling of the data management system, performing monitoring activities, and providing an electronic data capture solution (Secutrial database) for storage of participants’ CRF is done by the Clinical Trial Unit at the Geneva University Hospitals. In addition, statistical analysis is performed by the clinical trial unit (CTU) Geneva.

### Composition of the data monitoring committee, its role and reporting structure {21a}

The Safety Monitoring Committee (SMC) is constituted by 4 members, each being experts either in clinical trials or in the field of influenza and respiratory infectious diseases. One of the members is a statistician.

Task: Ensuring participant safety and detecting safety signals towards not giving antiviral is putting the patients in danger. The SMC first met before the start of the trial to discuss the protocol, the trial, and to have the opportunity to clarify any aspects. Further on, the SMC should meet once a year within 3 months after the end of each influenza season. The meetings and dates are set up by the sponsor in agreement with the SMC.

The Interim Data Report discussed after each influenza season includes only data containing potential safety signals: mortality, intensive care admission, and collected safety events according to the protocol. Data will remain blinded, with the lifting of the blind only at the request of the SMC.

After the second influenza season, on top of the data cited above, a sample size re-estimation will be performed to check the assumptions made on the median time to clinical improvement and the prevalence of patients with symptoms evolving for less than 72 h. There will not be an interim analysis, nor a futility analysis during the trial as their power would be insufficient. Depending on the data and for the sake of patients’ safety, the SMC may order additional analysis.

The SMC is independent of the sponsor, and its members do not have competing interests. A charter is available on request.

### Adverse event reporting and harms {22}

Baloxavir’s safety profile is well known and extremely favorable. Adverse events are not part of our study questions. Therefore, only serious adverse events considered unrelated to the natural history of influenza will be reported to the competent authorities in the annual safety report. SAR and SUSAR will be reported timely to the competent regulatory authorities.

### Frequency and plans for auditing trial conduct {23}

Monitoring is organized by the CTU Geneva. CTU Zurich and CTU EOC are involved in the monitoring of the Zurich and the Locarno-Lugano sites, respectively.

The monitoring strategy has been defined by the Clinical Trial Unit as low-risk, according to the SCTO guidelines and the Risk-Based Monitoring (RBM) Score Calculator published on https://www.sctoplatforms.ch/en/tools/risk-based-monitoring-score-calculator-31.html.

A site initiation visit was conducted before the inclusion of the first participant. During routine monitoring visits, the verifications concern: existence and completion of informed consent forms, eligibility criteria, primary outcome including the values necessary to calculate the last two NEWS2 scores before hospital discharge, influenza vaccination history, age, BMI, clinical status on day 7, investigational medicinal product dispensing and accountability, trial master file/investigator site file completeness, whenever necessary.

A close-out visit will be conducted at the end of the study. The study is considered as a low-risk trial; therefore, there is no Project Management Group, Trial Steering Group, or Data Monitoring Committee. Please find details about the Safety Monitoring Committee in paragraph 21a.

### Plans for communicating important protocol amendments to relevant parties (e.g., trial participants, ethical committees) {25}

Substantial amendments will only be implemented after approval of the competent ethics committee and the competent authority (Swissmedic), respectively. After approval by the competent authorities and before implementation, all substantial amendments are communicated to the funder. The revised protocol is then sent to the local PIs of all recruiting centers to be stored in the ISF. All substantial amendments will be communicated to participants of the study if they occurred during the length of their follow-up. A substantial amendment will also lead to an update of all trial registries (clinicaltrials.gov, NCTCP).

All non-substantial amendments will be communicated to the competent authority as soon as possible if applicable and to the competent ethics committee within the annual safety report. All non-substantial amendments are also communicated to the funder annually in the interim scientific report.

Protocol deviations are fully documented and collected in the dedicated deviation log in the trial master file as well as in the ISFs.

### Dissemination plans {31a}

Results will be published in a peer-reviewed open-access journal as an original article. The manuscript will be written by the PI and the project manager with the help of the study team. All authors will critically review the manuscript. We do not foresee the use of professional writers. We will grant public access to the full study protocol. Datasets originating from our project and used in case of the publication of our results will be deposited in the institutional open-access data repository: “Dryad” and will be made public at the time of the publication. Metadata will be searchable and discoverable.

Research results will also be communicated to the general public. We foresee research result publication in laymen’s terms during the year following the end of the study. We are going to involve patient partners in formulating a lay summary of the research results. We plan to publish in the hospital’s information magazine as well as in the form of a press release with the help of the HUG’s communication department.

